#### Evaluation of the national implementation

The implementation process will be evaluated, starting with the promotion of courses for clinicians, the degree of course participation, the adoption and fidelity of the implementation in the clinics, through to the potential impact on health care utilisation at a national level. An evaluation of sustained implementation is not part of this protocol. Elements of the process evaluation are listed in Table 3.

**Table 3 Tab3:** Overview of the aspects of the national implementation that are evaluated and the related measurement

Process	Definition/Measurement	Data Source
*Spread (promotion of GLA:D Back)* Newsletter from professional organisations Information to GLA:D Knee/Hip deliverers Description of GLA:D Back in magazine for general practitioners Information on the GLA:D Back web site Use of social media	The extent to which the intended promotion activities are delivered (Table 2)	Web sites, social media, e-mails
*Clinician reach*	The proportion of chiropractors and physiotherapists, on a contract with the universal health insurance, participating in GLA:D Back courses. Profile of enrolled clinicians.	Course registration
*Penetration and adoption (extent of implementation)*	Geographical penetration measured as the number of municipalities with at least one GLA:D Back deliverer. Rate of adoption will be measured as the proportion of clinics with trained clinicians offering GLA:D Back (defined as having entered at least five patients in the clinical registry) within 6 months of course participation. The number of patients starting GLA:D Back	GLA:D Back registry
*Fidelity (quality of implementation)*	The extent to which the core elements of the clinical intervention are delivered	Observations in selected clinics Patient 4 month surveys
*Determinants of implementation*	The domains of knowledge, skills, beliefs about capability, beliefs about consequences, innovation, patients, intentions, organisation, social influences, social context, and behavioural regulation are captured by the Determinants of Implementation Questionnaire (DIBQ) [16].	Clinician surveys
*Patient participation*	Proportion of patients enrolled in GLA:D Back that complete the program Profile of enrolled patients and of completers/non-completers Reasons that patients do not want to participate	Patient surveys in the GLA:D Back Registry Clinician surveys

Promotion of courses and pre-defined minimum standards for each element of the promotion strategy will be monitored during the roll-out (Table 2). A research team, not otherwise involved in GLA:D Back, will conduct the monitoring and provides feedback to the GLA:D Back project group at regular intervals, which in turn will determine the actions required when standards are not met. For example, if one region has less than 60 clinicians registered, this will be fed back to the project group with information on any particular clinician groups (e.g. related to professional background or clinical experience) that appears not to have been reached so that actions can then be taken to reach that specific group(s).

The adoption of GLA:D Back will be investigated by measuring the extent to which clinicians who have participated in the GLA:D Back course conduct the program in their clinics. Individual clinician factors and organisational factors will be investigated as determinants of adoption.

Fidelity will be investigated quantitatively by asking about treatment content and recall of key messages via patient questionnaires, and by ensuring that patients’ individual goals are registered. The quality of care in terms of delivering the key elements of the intervention will be further explored by video-based observations and from patient interviews that will provide a patient perspective on the content of care.

The profile of patients enrolled in the GLA:D Back programme will be compared between clinics and administrative regions to investigate if clinicians seem to agree on the target group as well as detect if regional politics or planning affects patient selection. Also, the proportion and profile of patients enrolled who do not complete the program will be compared across clinician profiles and regions. Finally, we will ask clinicians about their experience with patients being motivated to enrol in the program and the reasons why patients considered suitable candidates for the program declined participation.

The frequency of referrals to imaging and to secondary care for back pain, opioid prescription and long-term sick leave related to LBP at the national level will be compared between 2016 and 17 before implementation starts and during 2020–21, i.e. commencing one year after all Danish regions have had clinicians educated. Comparisons will be made at the overall population level as well as for populations with a history of LBP identified from sources such as The Danish National Health Survey.

### Outcome measures

Outcomes at the clinician level and patient level will be matched to the theoretical model of change in Fig. 3.

#### Outcomes of the clinical intervention

An overview of the study measures is provided in Table 4.

**Table 4 Tab4:** Overview of study measurements related to the clinical intervention

Construct	Instrument	Patient reported				Clinician reported		National registries
		Baseline	3-months	6-months	12-months	Pre- intervention	Post- intervention	
Demographics	Age, sex, height, weight, education	x						
Work situation	Job type, working hours	x						
Risk profile	The START Back screening tool	x						
LBP history	Pain duration (0–2 weeks; 2–4 weeks; 4–12 weeks; 3–12 months; > 1 year) Pain trajectory last 12 months (one of seven patterns or ‘I don’t recognise any of the patterns)	x						
Comorbid pain	Pain in any of nine regions on body chart in the last 2 weeks	x			x			
Comorbidity	Any chronic disease (yes/no) on a list of 15 conditions					x		
Illness perceptions	The Brief Illness Perceptions Questionnaire [42, 43]	x	x	x	x			
Ability to move with variation	How confident are you in performing exercises in a beneficial way?’ (0–10 scale from ‘not confident at all’ to ‘absolutely confident’)	x	x	x	x			
Physical back performance	Standing forward bending [46] The Ito back extensor endurance test [49, 50] Trunk flexor endurance test [50, 51] Sit-to-stand test					x	x	
Perceived physical fitness	Self-assessed physical capacity [57]	x	x	x	x			
Fear of movement	Fear Avoidance Beliefs Questionnaire [54, 56]	x	x	x	x			
Self-efficacy	The Arthritis Self-efficacy Scale (subscales pain + other symptoms) [59]	x	x	x	x			
Pain intensity	Numeric Rating Scale 0–10 for LBP and leg pain [64]	x	x	x	x			
Activity limitation	Oswestry Disability Index [62, 63]	x	x	x	x			
Quality of life	SF-36 general health, social functioning, mental health	x	x	x	x			
Work ability	Current work ability Number of days with LBP related sick leave within last 3 months	x	x	x	x			
Content of intervention	Received listed intervention yes/no		x					
Satisfaction	Overall are you satisfied with your course of care (5-point Likert scale)		x					
Harms	Did you experience any side effects or problems in relation to your participation in GLA:D Back?		x					
Back pain treatment	Consultations to general practice, chiropractors, physiotherapists and other clinicians due to back pain	x	x	x	x			
Health care utilisation	Reimbursed consultations to general practice, chiropractors and physiotherapists; Secondary care visits for back pain; Imaging for back pain Prescriptions for pain medication							x
Long-term sick leave	Number of reimbursed days with sick leave							x

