The study objectives for the evaluation of the clinical intervention are:To describe changes in patient outcomes after participation in GLA:D Back and evaluate if these are of a magnitude comparable with those observed in RCTs on combined patient education and exercise interventions for persistent and recurrent back pain,To determine to what extent patterns of health care utilisation and sick leave change in individuals from one year before participation in GLA:D Back to one year after,To determine if patient outcomes are associated with clinicians’ treatment orientation and confidence,To identify subgroups of patients who do not benefit sufficiently from the GLA:D Back clinical intervention, andTo investigate potential mechanisms of change in patient outcomes.

With respect to within subject changes we hypothesise that the clinical intervention is as effective as previously observed changes in RCTs on similar interventions.

The study objectives for the evaluation of the clinician educational intervention are:To monitor outcomes of learning activities and adapt the delivery of the clinician course accordingly,To determine if there is a change in treatment orientation from a biomedical to a more behavioural orientation and an increase in clinicians’ confidence in managing people with back pain following the GLA:D Back course,To identify clinician factors related to treatment orientation and confidence in managing back pain, andTo determine if treatment orientation and clinicians’ confidence are associated with clinical behaviours.

We hypothesize that the educational intervention is effective in preparing the clinicians to deliver the clinical intervention as intended.

The study objectives for the evaluation of the national implementation are:To monitor the promotion of GLA:D Back courses and adapt the promotion strategy when prespecified criteria are not met,To describe the penetration, adoption, and fidelity of GLA:D Back including the degree of uniformity across clinicians, clinics, and regions,To identify individual and organisational determinants of adoption and fidelity, andTo evaluate the effects of the implementation on referrals to imaging and secondary care for back pain, opioid prescription, and sick leave rates at the national level.

We hypothesize that in the long run the implementation will imply reductions in referrals to imaging and secondary care and in opioid prescriptions for back pain at the national level.

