**Fig. 3 Fig3:**
[figure not shown]
The theoretical model of change at the clinician level and the patient-level

Clinicians can adapt GLA:D Back to their particular setting and to the needs of individual patients, however, the following core parts cannot be altered: 1) an individual session at the beginning and the end of the program with goal-setting and physical tests, 2) 2 h of patient education and 16 sessions of supervised exercises over 8 to 10 weeks, 3) key messages stating that pain is not a sign of danger, 4) an explanation of back pain using a behavioural model of (im) balance between demands and capacity rather than emphasising tissue damage (Fig. 4), 5) guidance for patients in exploring movement rather than being taught to perform exercises in one ‘correct’ manner, and 6) entry of data into the clinical registry. Refinements of the content of the patient education or exercise program will be made continuously by the research group without violating these principles.

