Second, the main body of the course is aimed at developing participants’ ability to deliver the GLA:D Back clinical intervention as a way of addressing pain cognitions and behaviours by introducing all elements of the clinical intervention: goal-setting, clinical tests, patient education and supervised exercises. Goal-setting is introduced by presenting the SMART-model (Specific, Measurable, Acceptable, Realistic, and Time bound goals) [40]. Role plays to practice the use of explanatory models and skills training are used to become familiar with pain education, physical tests and exercises. Using some of the slides from the patient education material, participants work in groups taking turns to deliver key messages from the pain education to each other as they would in a real patient session, evaluated using peer feedback. The clinical tests and exercises are introduced in a practical session where tests are carried out on a colleague, and exercises are performed by the participants while examples of variations are presented. The supervision of exercises is practised in a session based on video cases and centred on the messages (spoken and unspoken) that can be delivered while supervising patients in the clinic. Key messages from the patient education should be reinforced during the instruction of exercises, for example, when explaining to patients how to cope with pain provocation during exercises rather than withdrawing from the activity. Finally, participants are introduced to the clinical registry used for data entry. At the end of Day 2, clinicians plan how and when to start GLA:D Back in their clinics. They are encouraged to pursue implementation by referring to the success of the GLA:D Knee/Hip model and the experience with GLA:D Back from pilot testing, as well as by emphasising the importance of physiotherapists and chiropractors taking on the role of ensuring access to evidence-based care for back pain.

Courses may be refined during the process of implementation, however, the core parts that are not subjects to change are: 1) familiarising participants with the key messages of the clinical intervention, 2) the introduction to the clinical registry, and 3) that the clinicians practice the delivery of patient education and the instruction of exercises during the course.

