#### Evaluation of the clinical intervention

The clinical intervention will be evaluated based on data about the patients who enrol in the GLA:D Back program, i.e. those patients who are registered in the GLA:D Back registry.

Due to the lack of a control group we will compare mean changes in these patients with those observed in the intervention groups of trials that have demonstrated positive effects of patient education and exercise therapy. We will look for trials with little risk of bias that included patient populations comparable with those enrolled in GLA:D Back.

Health care utilisation and sick leave will be investigated using national registry data to compare individual patterns of health care utilisation (primary care visits, hospital visits due to LBP, imaging for LBP, prescriptions for pain medication) and sick leave from 1 year before participation in GLA:D Back to 1 year after participation (Fig. 5).

Clinicians’ beliefs about back pain and confidence in managing patients with LBP (described below) and their baseline characteristics will be investigated as potential predictors of patient outcomes. Potential mechanisms of change in patients will be investigated by testing the mediating pathways outlined in the theoretical model (Fig. 3). We will specifically test the extent to which improved illness beliefs, increased perceived ability to perform exercises, and improvements on physical tests may explain a reduction in fear avoidance, improvement in expectations and increased self-assessed physical capacity during the 3 months after inclusion and during the following 3 months (3- to 6-months follow up). We will then test to what extent reduced fear avoidance beliefs, improved expectations and increased physical capacity during the initial 3 months relate to an increase in self-efficacy during the same period and to improved self-efficacy after 6 and 12 months. Next, we will investigate the relationship between increased self-efficacy and outcomes of self-management success, and whether self-efficacy is a mediator between beliefs and performance and success in self-management. Lastly, we will test to what extent improvements in disability, quality of life and pain after 6 months predict health care utilisation and sick leave after 12 months, to what extent improved self-efficacy influences these outcomes, and if this is fully or partly explained by improvements in self-management.

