##### Outcomes related to clinician behaviours

The delivery of a group-based patient education and exercise program will be assessed as the proportion of patients who reports participation in both of these activities. The delivery of key messages as part of the intervention will be measured as patients’ recall of having heard five key messages as part of their treatment course. Three of the listed messages are key messages in the GLA:D Back approach (‘Movement is healthy for the spine’, ‘Pain does not equal harm’, ‘Your brain has a memory for pain – like having a bad song stuck in your head’) and two are messages not in line with the intention of GLA:D Back (‘I need to avoid certain positions or movements’, ‘In my case, pain means I should stop what I am doing’). Both measures of delivery of care are included in the patient three-month follow up. Use of individual goals will be measured as the proportion of patients for whom a goal is described in the clinical registry.

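### The only harms item is one patient-attributed question at 3 months, in a programme that teaches that pain is not danger, and the article names no outcome that counts worsened patients

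*Protocol article*

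**What the plan says.** **Harms item.** Table 4, under Outcomes of the clinical intervention, has one row labelled Harms. It holds a single patient-reported question, marked for the 3-month survey only: "Did you experience any side effects or problems in relation to your participation in GLA:D Back".

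**Programme content.** The list of core parts that clinicians may not change includes "key messages stating that pain is not a sign of danger". The section on the clinician course says these messages should be reinforced during exercise, for example "when explaining to patients how to cope with pain provocation during exercises rather than withdrawing from the activity". Under Outcomes related to clinician behaviours, patients are asked whether they recall hearing "Pain does not equal harm". That question falls in the same survey wave as the harms item: "Both measures of delivery of care are included in the patient three-month follow up".

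**Effect summary.** Evaluation of the clinical intervention states, for want of a control group, that "we will compare mean changes in these patients with those observed in the intervention groups of trials". An objective in the Background is "To identify subgroups of patients who do not benefit sufficiently from the GLA:D Back clinical intervention".

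**Other data.** Table 4 also lists "Numeric Rating Scale 0–10 for LBP and leg pain", the Oswestry Disability Index, SF-36 subscales, work ability and sick-leave days due to back pain. All are taken at baseline, 3, 6 and 12 months, and none asks the patient for attribution. Registry data compare each person's care use, pain-medication prescriptions and sick leave in the year before and the year after participation.

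**The concern.** With exercise that may provoke pain, an obvious harm to look for is a flare or a lasting worsening of back or leg pain. Whether a patient calls that a side effect or problem of the programme depends on how the patient interprets pain, and the programme sets out to change that interpretation. A clinic that conveys the messages well could record fewer harms although the same number of patients got worse.

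A low rate on this item could then be read as reassurance about safety in a nationwide roll-out. A favourable mean change would not correct that reading, because a mean can improve while a sizeable minority deteriorates.

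**Working it through.** The plan gives no figure for harms or deterioration, so there is none to reproduce. The check has three parts.

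**1. What the harms item can and cannot show.**
- Asked once, at 3 months; no harms row at 6 or 12 months.
- Patient-reported only; Table 4 lists no clinician-reported harms.
- Tied to participation by its wording.
- Under Acceptability among patients, clinicians record whether the programme was completed, with no reason for stopping. The listed reasons concern patients who decline to join.

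The item therefore rests on a judgement that the core messages address. Later analysis cannot remove that dependence from the answers.

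**2. Whether any named outcome reports worsening.**
- The comparison with published trials is of means.
- The subgroup objective concerns insufficient benefit, which puts unchanged and worsened patients together.
- Table 4 contains the raw material (pain, disability and work at four time points), but the article states no deterioration outcome or threshold.

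**3. What a mean can conceal, and how precisely worsening could be reported.** Inputs from Sample size: 1500 patients, effect size 0.2, variance inflation factor (VIF) up to 5. Assumptions made here: effect size is mean change divided by the SD of change, the change is normal, and the margin for worsening is 0.5 SD. The value 0.5 for a larger effect is also an assumption.

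P(worse by more than 0.5 SD) = Φ(−(m + 0.5)), where m is the standardised mean improvement.

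| m | Calculation | Proportion | Of 1500 |
|---|---|---|---|
| 0.2 | Φ(−0.7) | 0.242 | 363 |
| 0.5 | Φ(−1.0) | 0.159 | 238 |

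Precision of an assumed 10% worsened, 95% half-width = 1.96 × √(p(1−p)/(1500/VIF)):
- VIF 1: 1.96 × √(0.09/1500) = 0.015, or 1.5 points.
- VIF 5: 1.96 × √(0.09/300) = 0.034, or 3.4 points.

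The planned sample could therefore report such a proportion usefully even under the heaviest clustering allowed for.

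**The case against.** The strongest reply is that the plan already holds what is needed. Pain, disability and work are measured repeatedly without attribution. Registry patterns are compared within individuals. Patient interviews and latent class models are planned, and one objective looks for patients who gain too little. Detailed analysis is left to subproject plans that are not shown, so a threshold may exist there. This is a type 3 hybrid study with no safety objective and no control group, so worsening could not be attributed to the programme in any case. Finally, the harms question is broad and open.

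Much of this stands. A reader might infer that worsening patients will be missed, or that nothing else in the plan could reveal them. The documents do not support that, because the data to find them are collected. A reader might also infer that every effect is reduced to a mean, but the mean-change statement concerns only the benchmark against trials. Nor is the omission of leg pain under Self-management success a gap in the outcome set: that section lists indicators of one construct, and leg pain is in Table 4.

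A reader might further take the downward bias as established. It is an inference from the programme's content, without a figure. Recall of the key messages is collected in the same survey, so the link could be examined.

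Two things remain. The wording, timing and attribution of the harms item are fixed in this article, so an unseen analysis plan cannot repair them. And collecting data that could show worsening is not the same as naming an outcome that reports it. The missing threshold is the weaker part, since it may be set elsewhere.

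**Conclusion.** The point holds in a limited form. A single attributed question at 3 months is a thin measure of harm in a programme that aims to change how patients interpret pain, and under-reporting of flares or lasting worsening is plausible. Its size is unknown. The article names no outcome that separates worsened patients from those who merely fail to improve, although the data would allow one.

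The 24% and 16% figures show only that a favourable mean is compatible with many worsened scores. They rest on an assumed normal change and an arbitrary margin, and they include natural course and measurement error. They do not estimate missed harm, and 0.2 is the effect the study is powered to show, not a forecast. This is a cheap improvement to reporting and does not invalidate the design.

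**What to change.** **Reporting.** Beside the mean changes and the harms item, report the proportion of patients worsened by a pre-set margin on the Oswestry Disability Index, the back-pain rating and the leg-pain rating at 3, 6 and 12 months versus baseline. Fix the margins before the data are examined, and give the number of responders at each time. Label the table as descriptive, including natural course and measurement error, and not attributable to the programme without a control group. The cost is one table from data already collected.

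**Survey item, if it can still be edited.** Ask first whether named problems occurred during the programme, such as a lasting increase in back pain, new or worse leg pain, or a fall or injury. Ask only then whether the patient attributes them to GLA:D Back. The harms figure will probably look less favourable, and a change during data collection breaks comparability between patients asked before and after it. If the item is already in use and cannot be changed, the table alone still helps, and the report should state that the harms rate depends on patient attribution.
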